### Evaluation at study inclusion (T0)

The evaluation at study inclusion will consist of clinical characteristics of the patient, underlying disease, disease responsible for ARF, and investigations usually performed at ICU admission of immunocompromised patients with ARF.

### Evaluations during study participation

Evaluations performed during study participation will consist of respiratory characteristics (respiratory rate, SpO2, oxygen flow or FiO2) every hour within the first 24 hours; data to assess the disease course on day 1, 2, 3, 4, 5, 6, 7, 14, and 28 (the worst value will be recorded); clinical data; results of investigations; and data on NIV tolerance and efficacy.

### Evaluation at the end of study participation

Evaluations performed at the end of study participation will consist of mortality on day 28, ICU length of stay, hospital length of stay, time on IMV, and mortality on day 180.

### Bias minimization strategies

#### Recruitment bias

Before randomization, no patients will receive humidified high-flow oxygenation. Severity of ARF will be only assessed with the oxygen flow need at randomization, through Venturi mask or nasal cannula. After randomization, patients will receive a humidified high-flow cannula according physician. Humidified high-flow cannula use will be recorded and analyzed.

We will include only patients with ARF but no circulatory failure at baseline (defined by the need of vasopressor over 0.3 μ g/Kg/min), to obtain a population of patients who have severe disease but do not meet the criteria for IMV. We will include consecutive immunocompromised patients, with no restrictions based on type of disease or treatment, in order the replicate usual ICU practice. Patients in whom HIV infection is the only cause of immunodeficiency will not be included since recent data show differences in outcomes between HIV-infected patients and patients with other causes of immune deficiency. HIV-infected patients with other immunocompromised disease will be included.

#### Patient management bias

We will use predefined NIV parameters, oxygen therapy parameters, and IMV criteria to standardize patient management.

### Non-invasive ventilation parameters

We will use the NIV settings recommended for the management of ARF, in pressure support ventilation. The mask most appropriate for the patient will be selected and adjusted to minimize leakage and pressure points. The level of inspiratory assistance will be increased gradually to obtain a tidal volume (V_T_) of 7 to 10 mL/Kg with a respiratory rate (RR) <25/min. The positive expiratory airway pressure will be increased from 2 to 10 cm H2O to obtain a FiO_2_ < 65%. The FiO_2_ value will be set to keep SpO_2_ > 90%. The inspiratory trigger will be set at the lowest possible value. The physician in charge of the patient will check that asynchronous cycles are kept to a minimum (number of asynchronous cycles/total number of cycles <10%). The ventilatory settings will be chosen based on continuous SpO_2_ monitoring and arterial blood gas values. NIV will be used for at least six hours within 24 hours for two days, in sessions of at least 30 to 45 minutes, with oxygen therapy in the intervals.

Criteria for weaning off NIV are as follows: resolution of the signs of respiratory distress, RR <25/min between NIV sessions, P/F >200 for 24 hours, or the patient refuses NIV and does not meet the criteria for IMV. In patients requiring NIV for longer than 12 out of 24 hours or over more than five days, the need for IMV should be evaluated and the level of NIV use considered excessive.

### Oxygen parameters

The oxygen flow rate delivered through a mask will be set to maintain SpO_2_ > 90%. The choice of the oxygen therapy system will be at the discretion of the physician.

For patients receiving oxygen through a mask, FIO2 will be estimated according to the oxygen delivery system and oxygen flow.

### Invasive mechanical ventilation criteria

The criteria for IMV are: severe hemodynamic instability (norepinephrine or epinephrine >0.5 μ g/Kg/min), cardiorespiratory arrest, ongoing myocardial infarction, severe encephalopathy (Glasgow Coma Scale score <11), severe airway secretion retention, worsening of respiratory distress (SpO_2_ < 92% or RR >40/min) regardless of the oxygen flow rate or use of accessory muscles of respiration, inability to maintain PaO_2_ > 65 mmHg with FiO_2_ > 0.6, dependency on NIV with inability to remain off NIV for longer than two hours, or >50% increase in the time on NIV from one day to the next (for example, six hours of NIV on D1 followed by more than nine hours on D2).

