### Randomization and study treatment

Eligible patients will be randomly assigned, in a 1:1 ratio, to one of the two treatment arms. Randomization will occur either at ICU admission or when the eligibility criteria are met if the patient was admitted for a reason other than ARF. Randomization will be performed via the website telemedicine cleanweb.aphp. After having completed the randomization webpage, the investigator will receive the treatment arm designation. Time zero will be defined by randomization time. Randomization will be stratified by center, oxygen flow rate at randomization (>or ≤9 L/min), and reason of immunosuppression (oncologic and hematologic malignancy or immunosuppressed treatment and solid organ transplantation). All the data will be notified in an e-CRF on the website telemedecine cleanweb.aphp.

In the early NIV group (intervention group), NIV sessions will be administered throughout the 24-hour cycle, with oxygen therapy sessions in the intervals, the objective being to maintain SpO_2_ > 92%. NIV would be given for at least six out of 24 hours during the first 24 hours. In the oxygen-only group (control group), continuous oxygen therapy will be provided to maintain SpO_2_ > 92%.

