### Statistical analysis

The analysis will be performed according to the intention-to-treat approach. We will use the chi-square test to compare 28-day mortality rates in the group managed with oxygen only and in the group managed with oxygen and early NIV. Randomization will be stratified on the underlying disease (hematological or solid malignancy versus other) and on ARF severity as assessed by the baseline oxygen flow rate (≤9 L /min versus >9 L/min to obtain SpO_2_ > 95% and/or resolution of the signs of respiratory distress). We will test for an interaction between the treatment effect and the underlying disease. If such an interaction is found, we will use the chi-square test to look for a treatment effect within the stratification subgroups. We will correct for the multiple comparisons using the Bonferroni test (error of first order 0.025). Similarly, we will look for an interaction between the treatment effect and baseline ARF severity. If such an interaction is found, we will use the chi-square test to look for a treatment effect within the stratification subgroups. We will correct for the multiple comparisons using the Bonferroni test (error of first order 0.025).

For the secondary evaluation criteria, we will use the chi-square test to compare the proportions of patients with treatment failure (defined by the need of IMV), and nosocomial infection in the two treatment arms. The procedure described above for potential subgroup analyses of the primary evaluation criterion will be used for these secondary evaluation criteria. Wilcoxon’s test will be performed to compare the number of organ failures (SOFA score) between the two arms 72 hours after study inclusion. Median hospital and ICU length of stay will be compared between the two arms using the Kaplan-Meier estimator, with discharge alive as the event of interest and death as the censoring event. Time on invasive mechanical ventilation will be compared between the two arms using the log-rank test.

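### The SpO2 target is >92% in one section and >90% in two others, and the >90% target overlaps the SpO2 <92% intubation criterion

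*Protocol article*

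**What the plan says.** Four sections of the protocol article state an SpO2 threshold for managing patients after randomization.

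- **Randomization and study treatment.** In the early NIV arm, NIV is given "with oxygen therapy sessions in the intervals, the objective being to maintain SpO_2_ > 92" percent. In the control arm, "continuous oxygen therapy will be provided to maintain SpO_2_ > 92" percent.
- **Non-invasive ventilation parameters.** "The FiO_2_ value will be set to keep SpO_2_ > 90" percent.
- **Oxygen parameters.** "The oxygen flow rate delivered through a mask will be set to maintain SpO_2_ > 90" percent. This sentence is not limited to one arm, and patients in both arms receive oxygen.
- **Invasive mechanical ventilation criteria.** One listed criterion is "worsening of respiratory distress (SpO_2_ < 92% or RR >40/min) regardless of the oxygen flow rate".

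The section Patient management bias states what these rules are for: "We will use predefined NIV parameters, oxygen therapy parameters, and IMV criteria to standardize patient management". The Statistical analysis section makes intubation an outcome by comparing the "proportions of patients with treatment failure (defined by the need of IMV") between the arms as a secondary criterion.

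**The concern.** There are two separate inconsistencies.

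The first is target against target. The same treatment, most plainly oxygen by mask in the control arm, is to be titrated to >92% by one section and to >90% by another. No section gives either figure precedence.

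The second is target against intubation criterion. A clinician who follows the parameter sections may hold a patient at 91% as intended, yet that reading lies below the SpO2 cut-off in the intubation list.

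What is at stake is how uniformly the intubation rule is applied. The trial is open label, and the article names predefined parameters and intubation criteria as its safeguard against differences in management. Need of invasive ventilation is a secondary endpoint, and avoiding it is the route by which early NIV is expected to lower mortality. Conflicting written instructions on oxygenation next to an intubation criterion also matter for the patients themselves.

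**Working it through.** No sample size, power or alpha figure is involved. The check compares the stated thresholds directly.

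**Inputs**

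- A: SpO2 >92%, both arms (Randomization and study treatment).
- B: SpO2 >90%, under NIV and for mask oxygen (Non-invasive ventilation parameters; Oxygen parameters).
- C: SpO2 <92%, taken literally as a cut-off (Invasive mechanical ventilation criteria).

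**Step 1: overlap of each target with the cut-off**

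- A and C: SpO2 >92 and SpO2 <92 have no value in common.
- B and C: SpO2 >90 and SpO2 <92 share the open interval from 90 to 92. The only whole number in it is 91.

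**Step 2: where the two targets disagree**

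B is met and A is not when SpO2 is >90 and ≤92, that is, at the whole-number readings 91 and 92.

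**Step 3: whole-number readings from 88% to 96%**

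| SpO2 (%) | On target, A (>92) | On target, B (>90) | Below cut-off, C (<92) |
|---|---|---|---|
| 88–90 | no | no | yes |
| 91 | no | yes | yes |
| 92 | no | yes | no |
| 93–96 | yes | yes | no |

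At 91% the three rules give three different answers. At 92% the two targets still disagree, but the cut-off is not reached. From 93% up, all the sections agree.

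**Step 4: is there a further target?**

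The Statistical analysis section also mentions an SpO2 of 95%, in the stratum ">9 L/min to obtain SpO_2_ > 95% and/or resolution of the signs of respiratory distress". That figure grades baseline oxygen need for stratification. It is not a treatment target and is not part of this inconsistency.

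**Step 5: does any wording settle the matter?**

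In the NIV arm, the >92% objective could be read as applying only to the oxygen intervals between NIV sessions. That would separate it from the >90% setting under NIV. It would not help with oxygen by mask, for which Oxygen parameters still says >90%. In the control arm no such reading is available.

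**The case against.** The strongest defence has four parts.

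1. **The cut-off has a condition attached.** The SpO2 figure stands in a parenthesis after worsening of respiratory distress, and the remark about flow may mean hypoxemia that persists at any flow. A stable patient at 91% with room to increase oxygen would then not qualify. This reading is reasonable, but the text does not state it. The neighbouring PaO2 criterion names an oxygen level (FiO2 >0.6), whereas the SpO2 criterion sets flow aside. Sites could read it either way. The clash between 91% and the cut-off therefore holds on the literal wording only. The disagreement between the two targets does not depend on it.

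2. **The rules can all be met together.** Both targets are lower bounds, so a patient kept above 92% satisfies every section and is not below the cut-off. This stands. It would be too strong to call the rules incompatible. The clash arises only when a site follows the parameter sections and not the randomization section, but the article does not tell sites to prefer either.

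3. **There is one trigger, and it is the same in both arms.** A reader might infer that each ICU would choose its own intubation trigger, or that intubation would come to depend on the arm. The documents support neither. The intubation list gives a single SpO2 cut-off, what varies is the titration target, and each pair of targets is the same in both arms. Randomization is stratified by center, so differences between centers in the target adopted should be broadly balanced. Knowledge of the arm can influence intubation in any open-label trial and would do so if every figure matched.

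4. **The primary analysis is untouched.** This also stands. It is an intention-to-treat chi-square test of 28-day mortality, which none of these thresholds defines.

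**Conclusion.** The SpO2 thresholds are inconsistent as written. This is a contradiction between stated figures, not detail left to a fuller document. The targets of >92% and >90% conflict for the same treatments without any interpretation being needed. The overlap of the >90% target with the <92% intubation cut-off holds on the literal wording of the criterion.

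The size is limited. The overlap is the interval between 90% and 92%, or 91% in whole-number readings. The article does not say how many patients would be held there, so no effect on the intubation rate can be calculated. It is tempting to say that all 374 patients are affected. The rules do apply to all of them, but that describes scope and not impact.

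The consequence is weaker standardisation of the management that leads to a secondary endpoint, together with unclear instructions at the bedside. Bias between the arms is not shown, and the primary endpoint's definition, alpha and power do not change. Which value is clinically right is not judged here.

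**What to change.** The sponsor should reconcile the SpO2 figures in four sections: Randomization and study treatment, Non-invasive ventilation parameters, Oxygen parameters, and Invasive mechanical ventilation criteria. The reconciled text should state which target governs, and how the SpO2 part of the intubation criterion is to be read alongside that target. The values and the form of the criterion are for the investigators to decide.

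The cost is a clarification letter to the 29 ICUs or a short amendment. No new data item is needed, because Table 1 already records intubation criteria in both groups. The Trial status section reports 162 patients included, so 374 − 162 = 212 were still to be enrolled when the article was written, and a clarification could apply to them. The date on which it takes effect should be recorded, so that intubations before and after it can be told apart.

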### End of the trial

Each patient will be in the trial for six months. Premature study withdrawal will be considered if one of the following occurs: death within the first 28 days, or if requested by the patient or next of kin. Patients withdrawn prematurely from the trial should undergo the procedures scheduled for the last trial visit, to the extent possible. Furthermore, the reason for premature trial withdrawal must be recorded both in the case-report form and in the source document.

### Statistical analysis

The analysis will be performed according to the intention-to-treat approach. We will use the chi-square test to compare 28-day mortality rates in the group managed with oxygen only and in the group managed with oxygen and early NIV. Randomization will be stratified on the underlying disease (hematological or solid malignancy versus other) and on ARF severity as assessed by the baseline oxygen flow rate (≤9 L /min versus >9 L/min to obtain SpO_2_ > 95% and/or resolution of the signs of respiratory distress). We will test for an interaction between the treatment effect and the underlying disease. If such an interaction is found, we will use the chi-square test to look for a treatment effect within the stratification subgroups. We will correct for the multiple comparisons using the Bonferroni test (error of first order 0.025). Similarly, we will look for an interaction between the treatment effect and baseline ARF severity. If such an interaction is found, we will use the chi-square test to look for a treatment effect within the stratification subgroups. We will correct for the multiple comparisons using the Bonferroni test (error of first order 0.025).

For the secondary evaluation criteria, we will use the chi-square test to compare the proportions of patients with treatment failure (defined by the need of IMV), and nosocomial infection in the two treatment arms. The procedure described above for potential subgroup analyses of the primary evaluation criterion will be used for these secondary evaluation criteria. Wilcoxon’s test will be performed to compare the number of organ failures (SOFA score) between the two arms 72 hours after study inclusion. Median hospital and ICU length of stay will be compared between the two arms using the Kaplan-Meier estimator, with discharge alive as the event of interest and death as the censoring event. Time on invasive mechanical ventilation will be compared between the two arms using the log-rank test.

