### Sample size estimation

Based on previous studies in the field and on evidence of declining mortality rates over the last decade among ICU patients with hematological or solid malignancies
[12, 13, 18, 19], we expect 28-day mortality rates of 20% in the early NIV arm and 35% in the oxygen-only arm. With alpha set at 0.05, 90% power, and the chi-square test, 187 patients are needed in each arm, totalling 374 patients in all. A single interim analysis to assess superiority is scheduled. The interim analysis will take place after inclusion of half the patients (n = 187). The criteria for premature study discontinuation based on the results of this single interim analysis will be those defined by O’Brien and Fleming
[20]. All tests will be two-sided. The statistical analysis will be performed using SAS 9.1.3 (SAS, Inc., Cary, NC, USA) (or a more recent version) or R.2.15.2 (R foundation for statistical computing, Vienna, Austria). (or a more recent version).

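### The primary chi-square test ignores the clinical strata used in randomisation, a small avoidable loss of precision, and the strata are described differently in two sections

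*Protocol article*

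**What the plan says.** The Statistical analysis section of the protocol article names the primary test: "We will use the chi-square test to compare 28-day mortality rates in the group managed with oxygen only" and in the early NIV group. Sample size estimation uses the same test: "With alpha set at 0.05, 90% power, and the chi-square test, 187 patients are needed in each arm, totalling 374 patients in all". It rests on this assumption: "we expect 28-day mortality rates of 20% in the early NIV arm and 35% in the oxygen-only arm". The stratification factors enter the analysis only through interaction tests and, if an interaction is found, chi-square tests within subgroups. They play no part in the primary comparison.

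The strata are described twice:

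- Randomization and study treatment: "Randomization will be stratified by center, oxygen flow rate at randomization", cut at 9 L/min, plus reason for immunosuppression. That makes three factors.
- Statistical analysis: "Randomization will be stratified on the underlying disease (hematological or solid malignancy versus other) and on ARF severity". That makes two factors, without center. Severity is still cut at 9 L/min, but the flow is now the one needed "to obtain SpO_2_ > 95% and/or resolution of the signs of respiratory distress".

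**The concern.** When randomisation balances the arms within strata that differ in mortality, the mortality difference between strata no longer adds to the variance of the treatment comparison. The plain chi-square still counts it. Its standard error is then too large, its p-value is conservative and some power is wasted.

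The Background supports treating the two clinical factors as prognostic. It says that mortality rises with the severity of the respiratory failure. It also gives mortality under invasive ventilation of up to 40% in transplant and immunosuppressive-treatment patients, against 60% in malignancy.

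The second issue is wording with a practical consequence. A patient on 8 L/min with an SpO2 of 93% is in the lower stratum if the flow being given counts. The same patient may be in the upper stratum if the flow needed to meet the additional condition counts. The severity stratum also defines a planned interaction test, so its definition should not be open to two readings.

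**Working it through.** **1. The plan's own figure.** Inputs from Sample size estimation: 35% against 20%, two-sided alpha 0.05, power 90%, chi-square test. With pooled variance and no continuity correction:

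n per arm = [1.96 × √(2 × 0.275 × 0.725) + 1.2816 × √(0.35 × 0.65 + 0.20 × 0.80)]² / 0.15² = (1.2377 + 0.7978)² / 0.0225 = 184.1, so 185.

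The stated 187 is reproduced within rounding; a final alpha of 0.048, assumed here for the last look, gives exactly 187. Power at 187 per arm: (0.15 × √187 − 1.2377) / 0.6225 = 1.307, which is 90.4%.

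**2. Why the chi-square is conservative.** Take four equal strata with mortality 10, 30, 40 and 60% in both arms (an assumption). The mean is 35%. The pooled variance is 0.35 × 0.65 = 0.2275. The mean within-stratum variance is (0.09 + 0.21 + 0.24 + 0.24) / 4 = 0.195. With balance inside strata the true variance is 0.195 / 0.2275 = 0.857 of what the test assumes. The effective critical value is 1.96 / √0.857 = 2.117, a true two-sided alpha of about 3.4%. Strata at 20/35/35/50% give a ratio of 0.9505 and an alpha of about 4.4%.

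**3. Simulation.** 374 patients, 1:1 within four strata (disease × flow), marginal mortality 35% against 20% for power and 35% in both arms for type I error, critical value 1.96, no interim look. The CMH statistic is Σ(x₁ₖ − n₁ₖtₖ/Nₖ) / √Σ[n₁ₖn₀ₖtₖ(Nₖ − tₖ) / (Nₖ²(Nₖ − 1))], where in stratum k x₁ₖ is the deaths in the NIV arm, tₖ all deaths, n₁ₖ and n₀ₖ the arm sizes and Nₖ their sum.

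The documents give no stratum mortalities or prevalences for eligible patients, so these are varied. The last column converts the power gain to patients: 374 × {[(1.96 + z(power CMH)) / (1.96 + z(power chi-square))]² − 1}.

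| Assumption | Type I error, chi-square / CMH | Power, chi-square / CMH | Extra patients |
|---|---|---|---|
| Odds ratios 1 and 1 | 5.0% / 5.0% | 90.4% / 90.4% | 0 |
| 1.5 and 1.5 | 4.65% / 4.8% | 91.0% / 91.2% | 3 |
| 2 and 2 | 4.6% / 5.1% | 91.1% / 91.7% | 9 |
| 2 and 3 | 4.1% / 4.9% | 91.3% / 92.5% | 18 |
| 3 and 3 | 3.65% / 4.9% | 91.7% / 93.2% | 24 |
| Control strata 20/35/35/50% | 4.5% / 5.1% | 91.1% / 91.7% | 9 |
| 15/30/40/55% | 3.9% / 4.8% | 91.4% / 92.6% | 18 |
| 10/30/40/60% | 3.5% / 5.0% | 92.0% / 93.8% | 30 |

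Odds-ratio rows: prognostic odds ratios for disease and flow, each factor present in 50%, 40,000 trials. With prevalences of 80% and 40%, the gain for odds ratios of 1.5 to 3 is 0.2 to 1.2 points and the chi-square's type I error 4.0% to 4.9%. Last three rows: 100,000 trials.

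Worked example, last row: [(1.96 + 1.5382) / (1.96 + 1.4051)]² = 1.081, and 374 × 0.081 = 30.

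**4. Center as a stratum.** 29 × 2 × 2 = 116 cells, and 374 / 116 = 3.2 patients per cell. Many cells would carry little or no information in a CMH test.

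**5. The two descriptions of the strata.**

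| | Randomization and study treatment | Statistical analysis |
|---|---|---|
| Center | listed | not listed |
| Flow cut | 9 L/min | 9 L/min |
| Flow meant | rate at randomisation | baseline rate, with the SpO2 >95% and/or relief-of-distress condition |
| Disease split | malignancy against immunosuppressive treatment or transplant | malignancy against other |

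**The case against.** The strongest reply is that a prespecified chi-square is simple and valid, and that the sample size was computed for it. It keeps at least 90% power in every scenario, and an adjusted sensitivity analysis may sit in an analysis plan that is not shown. All of that stands. A reader might infer an inflated type I error or an underpowered trial; the calculations show neither.

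A reader might also take the variance ratio in step 2 as a sample-size gain: 374 / (1 − 0.143) = 436 patients, or 374 / (1 − 0.049) = 393 in the mildest case. That is too large. It uses control-arm mortality only, while the reduction is smaller at the lower mortality of the NIV arm. Stratified randomisation has also already made the estimate itself more precise. The simulated power gains support about 30 extra patients at most.

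Three further inferences go beyond the documents:

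- The article gives no reason for the choice of strata. Their prognostic value is inferred from the Background, and its 40% and 60% figures concern invasively ventilated patients.
- The SpO2 values of >92% and >90% elsewhere are treatment targets, so they do not by themselves contradict a stratum definition. The section on recruitment bias also speaks of the oxygen flow needed at randomisation, which narrows the gap between the two descriptions.
- The plan ties the subgroup tests to the stratification subgroups. A severity test on a different grouping is a possible result of the ambiguous wording and is not something the plan states.

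**Conclusion.** The point holds as one of efficiency and consistency; it does not threaten the trial's validity. The chi-square has a true type I error of about 3.5% to 4.9% and gives up about 0.2 to 2 points of power, equivalent to roughly 3 to 30 patients. The direction is firm if the strata are prognostic.

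The size depends on assumed stratum mortalities and prevalences, and on near-exact balance within the four clinical strata. Blocks run separately within many center cells could leave looser balance, and the conservatism would then be smaller. If the factors are not prognostic, nothing is lost or gained.

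The mismatch in strata is certain from the text but confined to two items: center, and the added condition on the flow stratum. Both parts are worth correcting because correction is nearly free.

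**What to change.** - Make the primary test a CMH test stratified by oxygen flow and reason for immunosuppression, using the values entered on the randomisation page. Report the stratified risk difference with its confidence interval.
- Use the same test at the interim analysis.
- Keep the plain chi-square as a sensitivity analysis.
- Do not use center as a fixed stratum in the test. A random effect or a sensitivity analysis can cover it.
- Reconcile Randomization and study treatment with Statistical analysis on whether center is a stratum and on how the flow stratum is defined. Use the definition actually programmed in the randomisation page, and apply it to the severity interaction test as well.

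The cost is protocol and analysis-plan wording; both clinical strata are already collected. Timing matters: Trial status reports 162 patients included and the interim is set at 187, so 187 − 162 = 25 inclusions remained at that point. The change should be made and dated before any unblinded comparison.

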**Figure 1 Fig1:**
[figure not shown]
**Outcomes associated with the in-ICU use of non-invasive ventilation in immunocompromised patients.** Adapted from Azoulay E, ^13^.

This forest plot figure represents cohort studies or trials reporting both patients receiving oxygen or NIV. Studies are presented with first author name, year of publication (number of patients treated with oxygen only and number of patients receiving NIV and oxygen). Odd Ratio (OR and [95% CI] comparing mortality associated with the use of NIV.

These studies include: two randomized ICU trials comparing two strategies for managing immunocompromised patients with ARF (Antonelli and Hilbert)
[11, 12]; a 2004 prospective nonrandomized trial evaluating the impact of ARF in patients with hematological or solid malignancies (Azoulay)
[1]; an ICU study in non-intubated patients with ARF randomized to two different diagnostic strategies (Azoulay)
[13]; a retrospective study of ICU patients with ARF managed with oxygen only or NIV (Depuydt)
[14]; and a 2011 multicenter Italian observational ICU study of patients with hematological malignancies and ARF (Gristina)
[15].

This literature review shows no difference in mortality rates between patients managed with oxygen only and those given NIV. However, none of these studies provides a sufficient level of evidence. In addition, patients in whom ARF was combined with other organ failures were not separated from those with isolated ARF. This is an important point, as the risk of mortality is known to increase with the number of organ failures and the severity of the ARF. Overall, these studies suggest that NIV may be useful as a prophylactic treatment to obviate the need for IMV. In contrast, the use of NIV as an alternative to IMV in patients with severe ARF seems to adversely impact survival.

We have planned a multicenter randomized controlled trial in immunocompromised patients with ARF. This trial will be carried out in 29 specialized ICUs in France and Belgium (in teaching hospitals, community hospitals, and national cancer network hospitals) with high admission rates of immunocompromised patients. The study objective is to demonstrate that incorporating early NIV into the management strategy for patients with ARF who do not meet criteria for IMV improves survival compared to oxygen only.

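### The two follow-up subgroup tests use single-step Bonferroni at 0.025; this is valid, but Holm's step-down rule keeps the same family-wise error and is never less powerful, with a material gain only for sizeable opposite effects

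*Protocol article*

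**What the plan says.** The Statistical analysis section names two factors for interaction testing: "underlying disease (hematological or solid malignancy versus other") and "ARF severity as assessed by the baseline oxygen flow rate (≤9 L /min versus >9 L/min"). Each has two levels. For each factor the rule is: "If such an interaction is found, we will use the chi-square test to look for a treatment effect within the stratification subgroups". The correction follows: "We will correct for the multiple comparisons using the Bonferroni test (error of first order 0.025"). Both sentences appear twice, once per factor. The section then carries the same procedure over to two secondary criteria, need for invasive mechanical ventilation (IMV) and nosocomial infection.

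The procedure and its level are therefore both fixed in the article, and no step-down rule is given. Each subgroup is held to 0.025 whatever the other shows. Under Sample size estimation, "All tests will be two-sided", so an adverse effect in a subgroup can be declared as well as a benefit. The level of the interaction test is not stated.

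**The concern.** With two tests at an overall 0.05, single-step Bonferroni is dominated. A procedure with the same error guarantee makes all of its rejections and some more. The cases lost are those where one subgroup reaches p ≤ 0.025 and the other falls between 0.025 and 0.05.

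The subgroup tests run only after an interaction has been found. Effects in opposite directions are one of the situations that can trigger them, and they are the situation in which both subgroup nulls are false and the second test matters. What is at stake is the chance of confirming the second effect, in whichever direction it lies. The main 28-day mortality comparison is not at stake.

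**Working it through.** **The plan's own figures.**
- Subgroup level: 0.05 / 2 = 0.025, as stated. For two independent subgroups the chance of any false rejection is 1 − 0.975² = 0.0494.
- Sample size: "With alpha set at 0.05, 90% power, and the chi-square test, 187 patients are needed in each arm, totalling 374 patients in all", with "we expect 28-day mortality rates of 20% in the early NIV arm and 35% in the oxygen-only arm". The pooled two-sided formula is n = [1.960·√(2·0.275·0.725) + 1.282·√(0.35·0.65 + 0.20·0.80)]² / 0.15² = 184.1, so 185 per arm. An assumed O'Brien-Fleming inflation of 1.007 gives 185 × 1.007 = 186.3, so 187. Power at 187 per arm is 90.4%. These figures stand.

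**Error control of Holm.** If both nulls are true, a false rejection needs the smaller p ≤ 0.025, which has probability at most 2 × 0.025 = 0.05. If one null is true, a false rejection needs that p ≤ 0.05, which has probability at most 0.05. The family-wise limit is therefore the same. By simulation with both nulls true, any rejection occurs in 4.93% of trials under either rule without the interaction step, and in 2.15% under either rule with it.

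**Gain, by hand.** The subgroups share no patients, so their tests are independent. Ignoring the interaction step:

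P(Holm rejects B) = P(p_B ≤ 0.025) + P(0.025 < p_B ≤ 0.05) × P(p_A ≤ 0.025).

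Assume 187 patients in each subgroup, with mortality (oxygen to NIV) of 35% to 20% in A and 20% to 35% in B. Power in either subgroup is 0.522 at level 0.025 and 0.634 at level 0.05. Holm gives 0.522 + (0.634 − 0.522) × 0.522 = 0.580, against 0.522 for Bonferroni, a gain of about 6 points.

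**Gain, by simulation.** The runs used two-sided uncorrected chi-square tests in each subgroup and an interaction test at an assumed 0.05, with 400,000 trials per scenario. All subgroup sizes and rates are assumptions.

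| Mortality, oxygen → NIV: A; B | Patients A / B | B confirmed, Bonferroni → Holm | Gain (points) |
|---|---|---|---|
| 35→20; 20→35 | 187 / 187 | 51.9% → 58.0% | 6.1 |
| 35→20; 35→50 | 187 / 187 | 43.7% → 49.9% | 6.2 |
| 30→10; 40→55 | 187 / 187 | 41.2% → 51.7% | 10.5 |
| 30→15; 40→55 | 187 / 187 | 41.0% → 47.9% | 6.9 |
| 30→10; 40→55 | 280 / 94 | 24% → 30% | 6 |
| 35→20; 20→35 | 280 / 94 | 27.2% → 34.6% | 7.4 |
| 35→20; 35→50 | 300 / 74 | 17.7% → 23.1% | 5.4 |
| 35→20; 35→45 | 187 / 187 | 19.7% → 24.4% | 4.8 |
| 35→20; 35→40 | 187 / 187 | 6.3% → 8.6% | 2.3 |
| 35→10; 35→30 | 187 / 187 | 0.4% → 1.3% | 0.9 |
| 30→10; 40→30 | 187 / 187 | 0.2% → 0.4% | 0.2 |

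If only A responds (35→20; 35→35), the power for A is 29.7% and 29.9%. In the rows with 15-point harm, the chance of confirming both effects rises by about 7 to 12 points, for example from 27.6% to 39.7% in the first row. Setting the interaction level at 0.10 leaves the first row almost unchanged (52.2% to 58.4%). The absolute percentages move by up to about 3 points with the exact split of 187 patients between arms; the gain does not.

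**Cost.** If A benefits and B is truly null, Holm rejects B more often. Without the interaction step and with 35→20; 35→35, this is 0.025 + 0.025 × 0.527 = 3.8%, against 2.5%. With the step and with 30→10; 40→40, it rises from 1.3% to 2.4%. Both are below 5%.

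**Intervals.** Holm adds a rejection only when 0.025 < p ≤ 0.05. In those cases a 97.5% interval for the risk difference includes zero in more than four cases in five across these scenarios, while a 95% interval excludes it.

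**The case against.** Nothing here is stated wrongly. Two tests at 0.05/2 are valid, the section is coherent, and Bonferroni keeps test and 97.5% interval aligned, which is a fair reason to prefer it. All of that stands and sets the weight of the point.

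The size of the gain also depends on the scenario. The rows with a gain of 5 points or more need a harm of about 10 to 15 points in one subgroup. With equal halves, 30→10 and 40→55 average to 35% against 32.5%, close to no overall effect, whereas the design expects 35% against 20%. Interactions in which both subgroups benefit give a gain below 1 point. This stands too, so the largest row should not be read as typical.

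A reader might infer that the protocol itself foresees harm in its more severe stratum, because the Background says that "the use of NIV as an alternative to IMV in patients with severe ARF seems to adversely impact survival". The document does not support that. The sentence concerns NIV given in place of IMV. The Eligibility criteria exclude patients who need immediate IMV, and the Discussion separates early from late NIV. The severity factor here is oxygen flow above or below 9 L/min among patients who do not yet meet IMV criteria. The sentence also says nothing about malignancy versus other causes, where the same rule applies.

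What remains is that Holm is at least as powerful in every scenario at the same family-wise limit, and that the article fixes the weaker rule explicitly.

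**Conclusion.** The point holds as a minor, optional improvement. Single-step Bonferroni at 0.025 controls the error rate but gives up some power in the second subgroup, meaning the one with the larger p-value. The loss is about 5 to 10 points under an assumed 15-point harm opposite to a benefit, about 5 points under a 10-point harm, and about 0 to 2 points otherwise. Subgroup power stays modest under either rule: in the rows with 15-point harm, about 18% to 52% with Bonferroni and 23% to 58% with Holm.

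These sizes rest on assumed subgroup splits, mortality rates and an interaction level of 0.05. The dominance of Holm does not. It would be wrong to infer that the plan's correction is invalid, that it hides harm, or that the primary result is weakened.

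How many tests belong in the family is a separate question. Four tests at 0.025 across both factors could reach 0.10 before allowing for the interaction steps, and Holm within each factor neither repairs nor worsens that.

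**What to change.** In both places in the Statistical analysis section, and for the secondary criteria that reuse the procedure, replace the single-step correction with wording such as: the two subgroup p-values are assessed by Holm's step-down procedure, the smaller at 0.025 and, if it is significant, the other at 0.05.

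Report the risk difference in each subgroup with an ordinary 95% interval, labelled as not adjusted for multiplicity. Intervals at 97.5% would usually contradict the extra rejections that Holm allows.

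The change costs a sentence or two of analysis wording and touches no patients, data or procedures. Two downsides should be accepted knowingly: Holm has no equally simple simultaneous intervals, and a truly null second subgroup is rejected slightly more often, within the 5% limit. The article reports 162 of 374 patients included, so as it stands the wording can still be changed before the final analysis.
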